### Cost analysis

Methods and instruments used for cost data collection in the NIATx 200 study [1] will be adapted to assess the costs of administering the SCS. Systems consultants will keep detailed logs of contacts with clinics (based on an online tracking system developed for NIATx 200) to assess staff participation and fidelity to the protocol. We will estimate the cost of the intervention by assessing time spent by systems consultants and clinicians during the implementation phase and multiplying these estimates by appropriate wage rates based on averages available through the Wisconsin Department of Workforce Development. We will add any relevant non-personnel costs, such as travel to site visits, the cost of teleconferencing services, etc.

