Specific Aim 2 focuses on field-testing the SCS implementation strategy. The systems consultants’ approach to interacting with clinics is modelled after the coaching protocol used in NIATx 200, which included in-person site visits and regular follow-up through phone and email communication. Participating clinics will be paired with a systems consultant to work through the SCS over a 6-month period. Each clinic will designate one clinician to act as a clinic leader in working with the systems consultant. The clinic leader will host two site visits by the systems consultant and communicate with the consultant monthly during the 6-month follow-up consulting period via phone and email. The clinic leader will work with a clinic’s “change team”—a group of 2 to 6 other staff members involved in opioid prescribing to identify and implement systems changes to improve opioid prescribing processes. The consultant’s initial site visit will last about 2 hours. The consultant will start by presenting the latest research on balancing the benefits and risks of long-term opioid use. The visit will include reviewing information gathered by the change leader before the site visit as a result of conducting a walk-through exercise, in which the change leader follows the clinic process for refilling an opioid prescription for a current patient, step-by-step. The visit will also help the change team determine the best course for implementing aspects of the checklist, depending on the clinic’s own workflow. The systems consultant will help synthesize baseline information from the walk-through and other activities and facilitate a brainstorming session with the change team using nominal group technique [28]. The systems consultant and change team will envision how to implement the checklist, assessing any systemic barriers to implementation. The systems consultant and clinic leader will debrief to develop an implementation plan and schedule a second site visit to assess progress. Throughout the intervention period, the systems consultant will help the team implement ideas for change using Plan-Do-Study-Act change cycles [29] and maintain monthly email and phone contact with the clinic leader and change team to monitor implementation progress and offer advice. The systems consultant will also be available to discuss patient care issues (e.g. difficult cases) during monthly phone conferences, with all identifiable patient data removed beforehand.

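### The costing rule counts consultants' and clinicians' time, but the change team is made up of staff who need not be clinicians, so any non-clinician labour falls outside the pilot's cost estimate

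*Protocol article*

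**What the plan says.** All references are to the protocol article.

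- **Who is costed.** The Cost analysis section bases personnel cost on "assessing time spent by systems consultants and clinicians during the implementation phase", then values the hours by "multiplying these estimates by appropriate wage rates based on averages available through the Wisconsin Department of Workforce Development". Travel, teleconferencing and similar items are added: "We will add any relevant non-personnel costs".
- **Which instruments.** The same section opens by saying that "Methods and instruments used for cost data collection in the NIATx 200 study [1] will be adapted to assess the costs of administering the SCS". The content of those instruments is not shown. It adds that "Systems consultants will keep detailed logs of contacts with clinics", and gives the purpose of these logs as "to assess staff participation and fidelity to the protocol".
- **Who does the work.** The Specific Aim 2 text (under Preliminary studies) has each clinic name one clinician as leader. The leader works with "a group of 2 to 6 other staff members involved in opioid prescribing".
- **When the work is done.** The first site visit reviews "information gathered by the change leader before the site visit as a result of conducting a walk-through exercise". Plan-Do-Study-Act cycles then run throughout the intervention period, with two visits in all and routine contact monthly over 6 months.
- **Where cost is used.** Specific Aim 3 lists costs among the feasibility and acceptability assessments. Table 1 has the cost of the consulting intervention as an Implementation measure, next to hours of consulting delivered or received per provider.

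**The concern.** Two parts of the article describe the clinic's workforce in different terms. The Aim 2 text calls the leader a clinician and the rest of the team staff. The costing rule takes up only the first term. A nurse or physician assistant would presumably count as a clinician; a receptionist, scheduler or clinic manager presumably would not. If such people sit on a team, their hours have no place in the rule as worded.

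There is a related question about the record of hours. A log of contacts kept by the consultant shows what happened when the consultant was involved. The strategy also relies on work that the clinic does alone, namely the walk-through and the change cycles between monthly contacts.

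At stake is the accuracy of a named pilot outcome. Leaving out labour can only push the cost estimate down. Hours that are not collected during the 6-month period would have to be reconstructed later from memory.

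**Working it through.** The article states no hours, wage or cost figure, so there is nothing to reproduce. The check is a comparison of the text, followed by an illustration of size.

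**1. Persons costed against persons working**

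| Role in the Aim 2 text | Covered by the costing rule? |
|---|---|
| Systems consultant | Yes |
| Clinic leader (a designated clinician) | Yes |
| 2 to 6 other staff who are clinicians | Yes |
| 2 to 6 other staff who are not clinicians | No, as worded |

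**2. Hours described against hours worked**

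The article describes three hours measures: the consultants' contact logs (Cost analysis), the intervention hours delivered to clinic staff, taken from those logs (Qualitative data collection and analysis), and the consulting hours in Table 1. All three measure contact or consulting. None by itself records the walk-through or the team's work between contacts. The qualitative section also lists activity logs, but does not say who keeps them, what they hold or whether they feed the cost estimate.

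**3. Illustration of size, per clinic**

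From the article: two visits, the first of about 2 hours; monthly contact for 6 months; a team of T = 3 to 7 including the leader.

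Assumed: a second visit of 2 hours; monthly contact of c = 0.5 to 1 hour with the leader only; w = 0 to 4 hours of work per member per month between contacts; n non-clinicians on the team, where n is zero or half of the other members.

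- Total person-hours = consultant (4 + 6c) + visits 4T + leader's calls 6c + between contacts 6wT.
- Hours omitted under the literal rule = (4 + 6w) × n.

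Results:

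- If all members are clinicians, n = 0 and nothing is omitted.
- Lowest share with half of the others non-clinicians (T = 3, n = 1, c = 1, w = 0): total = 10 + 12 + 6 + 0 = 28; omitted = 4; 4/28 = 14%.
- Highest share with half of the others non-clinicians (T = 7, n = 3, c = 0.5, w = 4): total = 7 + 28 + 3 + 168 = 206; omitted = 28 × 3 = 84; 84/206 = 41%.

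The Aim 2 text elsewhere describes the monthly contact as being with the leader and the change team. If the whole team joins, the leader's 6c becomes 6cT and the omitted hours become (4 + 6c + 6w) × n. The low end is then (T = 3, c = 1, w = 0) 10/(10 + 12 + 18) = 25%. The high end is (T = 7, c = 0.5, w = 4) 93/(7 + 28 + 21 + 168) = 93/224 = 42%.

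These are shares of person-hours, not of cost. The share of cost depends on wages by role and on the non-personnel items, neither of which is given.

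**The case against.** The strongest reply has four parts.

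- **Clinicians' time is not limited to contacts.** A reader might infer that all work between contacts is left out, because the contact log is the only time record that the cost section describes. The text does not say so. The stated purpose of the log is participation and fidelity, and it is not named as the source of clinicians' hours. The costing rule covers clinicians' time throughout the implementation phase. If the change leader who does the walk-through is the designated clinician leader, the rule can include that time. This stands.
- **The instruments are not shown.** The adapted NIATx 200 cost instruments may collect staff time, and an article commonly leaves such detail to the full protocol. This also stands for the source of hours. It does not settle who is costed, because the article's own costing sentence names only two groups.
- **Non-clinicians are not confirmed on any team.** Administrative staff appear only in a question put to the advisory panel. The Evidence gap/opportunity section speaks of involving clinical staff, with physicians, nurses and physician assistants as examples. This stands: the omission is possible, not shown.
- **The consequence for the later trial.** A reader might infer that an understated pilot cost would tilt the later cost-effectiveness comparison in favour of this strategy. The Rationale section says that the future trial will itself assess costs and effects. The Milestones section names means, standard deviations and effect sizes as what the pilot supplies for the power calculation. The documents do not support the inference.

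**Conclusion.** The point holds in a limited form. The costing rule and the description of the change team do not match, and, read literally, the rule leaves out any team member who is not a clinician. The direction of the resulting bias is certain: it can only be downward. The size is unknown. It is zero if all members are clinicians. The 14% to 41% of person-hours (25% to 42% if the whole team joins the monthly contacts) rests on assumed hours and on half of the other members being non-clinicians. It is neither an estimate nor an upper limit.

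For time between contacts, the conclusion is weaker: the hours measures described in the article would not capture it by themselves, but the article does not exclude it and unseen instruments may record it. It would go too far to conclude that the strategy has been shown to look cheaper than it is.

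**What to change.** Reword the costing rule to cover the time of systems consultants and all change-team members, clinicians or not, each valued at the wage for their role. State that this includes time between contacts and the walk-through before the first visit.

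Name the source of those hours. If the adapted NIATx 200 instruments already collect them, saying so is enough. If not, the consultant can ask at each existing monthly contact for the hours spent by role since the last one, and enter them in the existing online log.

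The cost is a wording change and, if needed, one extra question per monthly contact. The downside is that recalled hours are approximate, and the resulting cost figure may be less favourable to the strategy.

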### Qualitative data collection and analysis

We will follow NIH guidelines for mixed-methods inquiry [50] to complement quantitative assessments of the feasibility, acceptability, quality, and preliminary effectiveness of the SCS. During the intervention, we will use a variety of qualitative methods, including document review, activity logs, debriefing conversations with the system consultants, and observations of interactions between the systems consultants and the clinic change teams. These methods are designed to help us identify the incentives, scheduling, delivery methods, and other processes and structures that will make the SCS useful for participating clinicians and manageable for the systems consultants. Post-intervention focus groups will be used to compare the experience of clinics that changed substantially versus those that did not. We will explore questions such as (1) What kinds of process changes were associated with improvement? (2) What factors helped providers and clinics make changes? (3) What were the barriers to improvement, and how were they addressed? (4) When the intervention did not work well, what was different?

We will apply a combination of directed and traditional content analysis [51] to answer the questions posed above. Our analysis will identify themes in the qualitative data and organize them into a conceptual model that incorporates a priori elements of self-determination theory (e.g. relatedness, competence, autonomy) and diffusion of innovations theory (e.g. homophily), while simultaneously seeking new insights inductively.

Our second objective in this mixed methods component of our research is to assess fidelity to the intervention, defined as: (1) amount of the intervention received (i.e. ‘dose’), (2) adherence to the protocol, and (3) quality of intervention delivery [52]. Assessing the dose of intervention received will rely on quantitative data (the number of intervention hours delivered to clinic staff) obtained through logs kept by the systems consultants. For adherence, we will review the planned protocol with clinicians and document adaptations made to it at each site. To assess quality, we will examine both quantitative data on clinic-wide practices and focus group data on changes in clinicians’ prescribing attitudes and actions.

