Specific Aim 3 uses mixed methods to understand how the strategy worked, including assessments of feasibility and acceptability (costs, ease of recruitment, fidelity to the protocol, physician acceptance) and preliminary effectiveness (degree of checklist implementation, effect of the strategy on variation in opioid prescribing rates and dosing levels). While multiple prescribers (primary care physicians, nurse practitioners, physician assistants) potentially practice within each clinic, the clinic will serve as the primary unit of analysis. Relevant comparisons for study measures will be made in two ways. First, historical data are available for many study measures, permitting time-series analysis of repeated measures to detect changes in a clinic over time (pre-intervention vs. post-intervention). Second, we can compare intervention and control clinics per the matched-pairs design.

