### Milestones and products of pilot test

The primary goal of this project is to obtain pilot data for a large-scale clinical trial of different approaches to EBP adoption in healthcare. The research will be critical in developing (1) specifics of the guideline to be implemented, and (2) supports provided via the SCS implementation strategy and the systems consultants who deliver it. The protocol will be determined to be feasible if we enroll four intervention clinics, deliver the intended intervention in all four clinics, follow the clinics for a 6-month period, and obtain quantitative and qualitative data from participating clinicians. Acceptability will be gauged by assessing fidelity to the protocol and analysing qualitative data collected by the research team. We will continue to track effectiveness measures through the end of the 3-year grant period using de-identified electronic health records (e.g. opioid prescribing rate by clinician, number of treatment agreements signed) to assess the preliminary effectiveness of the SCS on clinical practice. With eight clinics reporting data (four intervention and four control clinics), we will be able to obtain baseline estimates of means and standard deviations for RE-AIM outcomes and point estimates of treatment effect sizes, thereby equipping us to conduct an accurate power calculation for the follow-up randomized trial.

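### Quality of delivery, one of three fidelity components, is to be judged from how clinics responded rather than from how the consultation was delivered

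*Protocol article*

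**What the plan says.** The section on qualitative data collection and analysis defines fidelity to the intervention in three parts: the amount received, then "2) adherence to the protocol, and (3) quality of intervention delivery". It gives each part a source.

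- **Dose:** intervention hours, "obtained through logs kept by the systems consultants".
- **Adherence:** "For adherence, we will review the planned protocol with clinicians and document adaptations made to it at each site".
- **Quality:** "To assess quality, we will examine both quantitative data on clinic-wide practices and focus group data on changes in" clinicians' "prescribing attitudes and actions".

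Earlier in that section the article plans document review, activity logs, debriefings with the consultants and "observations of interactions between the systems consultants and the clinic change teams". Their stated purpose is to find out what makes the strategy useful to clinicians and manageable for consultants. They are not named as sources for the quality component.

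The paragraph on Specific Aim 3 (under Clinic recruitment) lists fidelity with feasibility and acceptability. It describes the other side as "preliminary effectiveness (degree of checklist implementation, effect of the strategy on variation in opioid prescribing rates and dosing levels". Under Milestones and products of pilot test: "Acceptability will be gauged by assessing fidelity to the protocol and analysing qualitative data collected by the research team".

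**The concern.** Quality of delivery is a property of what the consultant does: how the site visits are run, how the walk-through findings are used, how the group session is facilitated, and how the change cycles are supported. The two sources named for it describe what the clinic does afterwards. A measure built on them records response under the label of delivery.

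This matters because the pilot is meant to shape the strategy, and the consultants' part in it, before a large trial. The article itself asks what was different where the intervention did not work well. If a clinic received its hours and the protocol was followed but prescribing did not move, the next question is whether the consultation was done poorly or was done well without effect. A quality assessment drawn from the absence of change cannot answer that. In the other direction, the Limitations section accepts that prescribing may fall through secular trends. Read through this component, such a fall could look like good delivery.

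**Working it through.** No arithmetic applies. The check sets each construct beside the source the article gives it and asks whether that source describes delivery or response.

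| Construct | Source in the protocol article | Describes | Shared with effectiveness? |
|---|---|---|---|
| Dose | Hours in consultant logs (Qualitative data collection and analysis; also Cost analysis and Table 1, Implementation) | Delivery | No |
| Adherence | Protocol review with clinicians and adaptations recorded by site (same section; also Table 1, Implementation) | Delivery | No |
| Quality of delivery | Clinic-wide practice data; focus-group data on change in prescribing attitudes and actions | Response | Yes |
| Preliminary effectiveness | Checklist implementation, variation in prescribing rates and dosing (Specific Aim 3); prescribing rates and pain agreements, among others (Table 1); prescribing rate and signed treatment agreements from health records (Milestones) | Response | n/a |

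**Step 1: does the quality source overlap effectiveness?** The article does not itemise clinic-wide practices. The practice data it describes elsewhere, such as prescribing rates, urine drug screens and signed agreements, are listed under effectiveness, and Specific Aim 3 puts checklist implementation there too. The focus-group source is explicitly about change in prescribing. Neither is a record of the consultant's conduct.

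**Step 2: how much of fidelity is affected?** One component of three. The other two would show low hours, missed contacts or departures from protocol whatever happened to prescribing.

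**Step 3: what is confounded?** Take two clinics with the same hours, the same adherence and visits of the same standard, where one changes its prescribing and the other does not. Delivery was equal. The named sources differ between the clinics only because the response differed, so an assessment resting on them would tend to rate delivery differently. The confounding is therefore conditional: it concerns quality once dose and adherence are adequate.

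**Step 4: does it reach acceptability?** The acceptability criterion refers to fidelity to the protocol. The three-part definition is of fidelity to the intervention, with adherence to the protocol as one part. The Cost analysis section uses the former phrase for what contact logs assess. If the acceptability criterion means all three parts, response data enter acceptability through quality. If it means adherence, or adherence and dose, they do not. The text does not settle this.

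**Step 5: is better material already planned?** Yes. The observations, activity logs and debriefings are in the same section, and Table 1 lists a structured clinic-lead interview on the consistency of consulting. None of these depends on prescribing change.

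**The case against.** The strongest reply is that the plan already holds ample evidence on delivery that does not depend on outcomes: hours per provider, adaptations, contact logs, the clinic-lead interview, observations and debriefings. A reader might infer from the quality sentence that fidelity, acceptability and effectiveness all rest on the same data, or that the pilot cannot tell poor delivery from an ineffective strategy at all. The document does not support either reading. Dose and adherence are independent of outcome, and acceptability also draws on other qualitative data.

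Three further points stand.

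- The article says the data will be examined. It describes no score or rule that turns prescribing change into a delivery rating, so agreement between quality and effect is a tendency, not a matter of definition.
- No analysis of fidelity against outcome is described, and no decision to proceed is tied to this component. Feasibility is judged by enrolment, delivery in all four clinics, 6-month follow-up and data obtained.
- Control clinics offer partial protection against reading secular change as effect, as the Limitations section says.

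It can also be said that an article leaves rating instruments to the full protocol. That is fair for a form or a scale. It does not answer the point here, because the article does name the sources for quality, and they are sources for something else. The clinic-lead interview does not fill the gap as written: it is aimed at consistency, which is not the same as quality, and it is not assigned to this component.

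**Conclusion.** The point holds in a limited form. One of three fidelity components, quality of delivery, is given sources that describe clinic response and overlap the effectiveness measures. Given adequate dose and adherence, that component cannot separate poor delivery from an ineffective strategy. It applies to all four intervention clinics. Dose and adherence are sound. Acceptability is touched only if its fidelity criterion includes quality.

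The conclusion rests on two readings: that clinic-wide practices means the kind of practice data the article lists under effectiveness, and that the two sources named for quality are the ones to be used for it. If the full protocol already assigns the observations and debriefings to quality, the article's sentence only needs to say so. A reader might go further and infer that the case for the large trial depends on a circular measure. The article ties no such decision to this component.

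**What to change.** In the fidelity paragraph of the qualitative section, name as sources for quality of delivery the observations of consultants with change teams, the activity logs, the consultant debriefings and the clinic-lead interview on consistency in Table 1. Judge this material against the consulting steps set out for Specific Aim 2 (site visits, use of the walk-through, the group session, the implementation plan, support for change cycles and monthly contact). Where practical, make the judgement before the clinic's prescribing results are seen. Keep practice data and change in prescribing attitudes and actions under effectiveness only. In the Milestones section, state which fidelity components the acceptability criterion uses.

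The cost is a few changed sentences and a small amount of extra qualitative coding. No new data source is needed.
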